### Assignment of intervention

Participants confirmed as eligible will be randomized at a ratio of 1:1:1 to each group in blocks of four participants until complete the total number calculated (*n* = 48). A computer-generated random numerical sequence will be used for randomizing participants (Research Randomizer). The principal researcher will generate the sequence and conceal it in sealed, numbered opaque envelopes. Participants will be allocated a sequential number upon screening. The sealed envelope corresponding to the allocated participant number will be opened on the first visit by the principal researcher, and the participants will be allocated, without knowing which group they will belong to. As this is a single-blind study, blinding is not required for principal researcher, only to participants. A Consolidated Standards of Reporting Trials (CONSORT) flow chart outlining the study phases is displayed in Figure 2 (Moher et al., 2001).

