### Study outcomes

The main outcome will be hemoglobin A1c levels after 8 weeks of interventions. A set of secondary clinical outcomes will include complete blood count with hemoglobin and reticulocytes, fasting glucose, fasting insulin, HOMA-IR, total-, LDL- and HDL-cholesterol levels, triglycerides, C-reactive protein, serum HIF1-α levels, systolic and diastolic blood pressure, body composition, cardiorespiratory and pulmonary gas-exchange variables. These outcomes will be evaluated at baseline and at the end of the study (eighth week), in all groups.

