### Statistical considerations

For sample and power calculations, this study is powered based on changes in hemoglobin A1c in RCTs included in the meta-analysis by Zuuren et al. (2018), which tested the effect of carbohydrate restriction up to 8 weeks. Considering a type I error of 5% and a power of 80% to detect differences at the dependent variable with a statistical significance when comparing 3 independent groups (CTRL versus EH and EH versus EH + LCD), and an effect size of 1.14, a sample size of 14 participants per group will be needed, totaling 42 individuals. With an assumption of a 20% dropout rate, we will recruit 48 participants. The sample size calculations were performed using the Statistical Power Analyses for Windows, (G*Power 3.1.9.4, Uni Kiel, Germany).

Statistical analysis will be performed using SPSS statistics software version 28.0, 2021 (IBM Company, Chicago, United States). All data will be reported as mean ± SD and statistical significance will be assumed at *p* ≤ 0.05. Pairwise comparisons will be analyzed using the Wilcoxon test. A two-way repeated measures ANOVA will be used to examine changes in cardiopulmonary parameters, body composition, glycemic profile, and cardiovascular risk factors over the chronic exercise period (0 vs. 8 weeks), and whether the magnitude of the chronic exercise-mediated adaptations differ between groups (EH vs. CTRL; LCD + EH vs. EH). When a significant main- or interaction-effect will be found, Bonferroni post hoc tests for multiple pairwise comparisons will be performed to identify differences between groups.

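### For HbA1c, Bonferroni post hoc tests leave each of the two named contrasts at about 0.69 to 0.75 power, below the stated 80%; a one-sentence change to Holm or a treatment-gated closed test recovers part or all of this at the same error rate

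*Protocol article*

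**What the plan says.** All of this is in the Protocol article. Study outcomes fixes the primary endpoint: "The main outcome will be hemoglobin A1c levels after 8 weeks of interventions".

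Under Statistical considerations, the sample size paragraph works at "Considering a type I error of 5% and a power of 80% to detect differences at the dependent variable", "when comparing 3 independent groups (CTRL versus EH and EH versus EH + LCD"), and concludes with "an effect size of 1.14, a sample size of 14 participants per group will be needed, totaling 42 individuals". It then adds: "With an assumption of a 20% dropout rate, we will recruit 48 participants".

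The analysis paragraph applies a two-way repeated measures ANOVA (0 versus 8 weeks, by group) to the glycaemic profile among other outcomes, and names the same two contrasts again. If a main effect or the interaction is significant, "Bonferroni post hoc tests for multiple pairwise comparisons will be performed to identify differences between groups". The number of comparisons in the Bonferroni family is not given.

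**The concern.** Two questions are planned, and the trial is sized for them. The analysis then applies a correction that the sample size does not carry, and that correction is not the most powerful valid choice for this design. With two planned contrasts, Holm is never less powerful than Bonferroni over the two. With exactly three arms, a significant overall treatment test allows each pair to be tested at an unadjusted 5% with family-wise error still controlled.

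At stake is power on the primary endpoint. The trial has 14 evaluable patients per arm by plan, and the article's own limitations section expects that a difference between EH and EH + LCD may be hard to show.

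**Working it through.** **Inputs.** From Statistical considerations: α = 0.05, effect size d = 1.14 (read as the standardised difference for one contrast), n = 14 per group, two named contrasts. Assumed: normal change scores, common SD, two-sided pooled-variance t-tests. With two time points, the group-by-time F test equals a one-way F test on change scores, here with 2 and 39 degrees of freedom.

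**1. The stated sample size.** The noncentrality is d·√(n/2).
- n = 14: 1.14 × √7 = 3.016; 26 df; critical t = 2.056; power 0.827.
- n = 13: 1.14 × √6.5 = 2.906; 24 df; critical t = 2.064; power 0.796.

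The smallest n reaching 80% is therefore 14, as stated, with no multiplicity adjustment. The same calculation gives 16 per group at 0.025 and 18 per group at 0.0167.

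**2. Power with the planned correction**, 14 per arm, variance pooled over three arms (39 df), post hoc step already open:
- Two-sided 0.05: critical t 2.023, power 0.837.
- 0.05/2 = 0.025: critical t 2.331, power 0.751.
- 0.05/3 = 0.0167: critical t 2.502, power 0.695.

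**3. The four rules compared by simulation** (400,000 runs per pattern, 14 per arm). Means are in SD of change for CTRL, EH, EH + LCD. The figure is power for a contrast whose true size is 1.14. The Bonferroni columns use the narrowest gate (interaction only); when a time effect opens the step they rise to the values in step 2.

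| Means | Bonferroni, 3 pairs | Bonferroni, 2 contrasts | Holm on 2, no gate | Interaction gate, then 5% each |
|---|---|---|---|---|
| 0, 1.14, 2.28 | 0.70 | 0.75 | 0.82–0.83 | 0.84 |
| 0, 1.14, 1.14 | 0.69 | 0.74 | 0.75 | 0.80 |
| 0, 0, 1.14 | 0.69–0.70 | 0.74 | 0.75 | 0.80 |
| 0, 1.14, 0.57 | 0.69 | 0.72 | 0.76 | 0.73 |

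In the first pattern, power to show both contrasts is 0.44 with Bonferroni over three pairs and 0.68 with the gated rule.

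Other sample sizes, Bonferroni over three pairs against the gated rule (midway pattern aside): 13 per arm (16 × 0.8 = 12.8), 0.65 against 0.76–0.81; 16 per arm (no dropout), 0.77 against 0.86–0.88.

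**4. Family-wise error, all arms changing equally.**
- Holm on the two contrasts: about 4.6–4.7%.
- Interaction gate, then unadjusted tests: about 4.2–4.3% over the two contrasts, 5.0% over three pairs.
- Gate as written, opened by a time effect, then unadjusted tests: about 9% over the two contrasts, 12% over three pairs. A simulated group-by-time ANOVA (assumed pre–post correlation 0.7) gave 10% over three pairs for a time effect of 0.3 SD and 12% for 0.5 SD or more.
- The same gate with Bonferroni over three pairs: about 4.3% over three pairs.

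**5. Why the interaction gate suffices with three arms.** If any two of the three pairwise null hypotheses are true, all three means are equal. The closed test of a pair therefore needs only the overall treatment test and that pair's own test, each at 5%. When exactly one pair is null, its false rejection rate is 5.0%.

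**The case against.** **A reader might infer that Bonferroni is redundant here** because a three-group test must be passed first. The text does not support that. Its gate is any significant main effect or interaction, and every arm exercises for 8 weeks, so a time effect is plausible and would open the step by itself. Under that gate Bonferroni is what controls the error (step 4). This objection stands in full: deleting Bonferroni without changing the gate would make the plan worse.

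**A reader might take the loss as certainly that of three pairs.** That is the natural reading of multiple pairwise comparisons, but the paragraph names only two contrasts, twice. The range 0.69–0.75 covers both readings. If the family is two, Holm gains little when only one contrast is real, and the gated rule at 0.73 in the midway pattern does not beat Bonferroni at 0.72–0.75.

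**The analysis paragraph also assigns pairwise comparisons to a Wilcoxon test.** The figures above assume t-tests and would shift somewhat with a rank test. This limits their precision, not the ordering of Bonferroni and Holm.

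**Bonferroni after ANOVA is valid and conventional.** True: it neither biases estimates nor inflates error. The point is one of efficiency. It is worth raising because the protocol fixes the rule itself, and the rule takes the trial below its own stated power.

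**Conclusion.** The plan as written gives each named HbA1c contrast about 0.69–0.70 power (family of three) or 0.72–0.75 (family of two) at d = 1.14 with 14 completers per arm, against a stated 80%. Holm on the two contrasts gives 0.75–0.83. A closed test gated on the treatment effect gives 0.80–0.84 in most patterns and 0.73 when the third arm lies midway. Both keep family-wise error at or below 5%.

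Two limits apply. Neither alternative guarantees 80% in every pattern of means. And the documents do not support calling Bonferroni unnecessary under the present gate. The figures rest on the stated effect size, normal change scores with a common SD, and pooled-variance t-tests. This is a cheap, worthwhile improvement, not an error that invalidates the analysis.

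**What to change.** Before any comparison between arms is seen, replace the Bonferroni sentence, for HbA1c, with one of these:

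- **(a) Holm, no gate.** CTRL versus EH and EH versus EH + LCD are compared on change in HbA1c; the smaller p-value is tested at 0.025 and, if significant, the other at 0.05. No ANOVA result is required first.
- **(b) Closed test.** The group-by-time (treatment) test is made at 5%. Only if it is significant is each of the two named contrasts tested at 5% without further adjustment. A main effect of time never opens these tests.

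Option (a) is the simpler rule and is never weaker than Bonferroni over the two contrasts. Option (b) is stronger in most patterns but depends on where the third arm lies. Either sentence should name the test used for the contrasts, so that it is not confused with the Wilcoxon sentence.

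The cost is one sentence; no patients or data are needed. The downside is that 95% intervals for the two contrasts are per contrast, not simultaneous. If Bonferroni is kept, state its family size and size the trial for it: 16 completers per group for two contrasts or 18 for three pairs, against 16 per group recruited before dropout.

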### Data collection and management

A questionnaire will be applied in the first nutrition appointment, at the beginning of the study, to obtain the eating habits, socio-demographic and clinical characteristics of participants, including age, sex, marital status, schooling level, diabetes duration, family history of diabetes and self-reported physical activity. Drugs for T2DM or comorbidities and nutritional supplements will be registered at baseline and at the end of the study.

Blood samples will be collected and centrifuged at 1000 g for 10 min to separate plasma or serum, which will be stored at −80 °C for further analysis of biochemical parameters.

During the intervention period, the team of researchers will be trained to apply the 24-h food recall, constantly checked the oxygen saturation and supervise the maintenance of the heart rate at the target intensity of 75% of the heart rate reserve. All researchers will be trained to circumvent any cases of hypoglycemia, hypotension or possible side effects of high-altitude exposure, such as headache or difficulty breathing. Also, it will be qualitatively documented and details of each case of withdrawal and, the primary hypothesis will be tested on a superiority framework.

All data will be collected and stored according to Good Clinical Practice Guidelines (Switula, 2000). Data monitoring and auditing of the trial will be conducted by the principal researcher and supervisory team: [name], [name] and [name] All data, such as consent forms, questionaries, dietary screening forms, IPAQ and clinical data in general, will be stored in a secure database password-protected document that will be accessed only by authorized members of the research team. Dietary plans will be stored securely in Dietbox® Software, and all information will be treated confidentially. Data will only be used for the purpose of this research project.

### Ethical considerations

The study was approved by the Ethics Committee of the Faculty of Nutrition and Food Sciences, University of Porto (Approval Number 45/2021/CEFCNAUP/2021 – Supplementary Material) in July 2021, and will be conducted in accordance to the declaration of Helsinki for studies in human (World Medical, 2013). It has been registered in the Clinical Trial Database (NCT05094505), and any important protocol modifications will be recorded on it. The study strictly follows the protocols regarding informed consent form, confidentiality and anonymity. An informed consent form with guidelines, objectives of the project, description of procedures, possible risks and benefits will be provided. Participants will also be informed that participation is voluntary, and they can withdraw from the study at any time, without prejudice. In addition, if requested, participants can access their individual data at the completion of the trial by contacting the lead researcher.

### Dissemination policy

The results from this study will be published in a peer-reviewed and open-access academic journal or in an open-access institutional repository. Participants in the trial will also be notified of the outcomes.

## Summary

This RCT aims to compare the effects of 8 weeks of EH (simulated high-altitude at 3.000 m), combined or not with an LCD (40% of energy from carbohydrates) on glycemic and lipid profiles, HIF1-α, C-reactive protein, blood pressure, body composition and cardiorespiratory parameters in patients with T2DM. The metabolic benefits of the 8-week duration of both interventions alone have been previously demonstrated in T2DM (Boule et al., 2001; Maiorana et al., 2002; van Zuuren et al., 2018)

These non-pharmacological treatments (LCD and EH) can improve T2DM control and prevent chronic complications due to uncontrolled glycemia and impaired vascularization (Ladage et al., 2012; van Zuuren et al., 2018). Several authors have shown beneficial effects on T2DM in people who following a LCD, mainly in the short-term intervention (Sainsbury et al., 2018; Snorgaard et al., 2017). Sainsbury et al. (Sainsbury et al., 2018) showed that restricting carbohydrates to less than 26% of total energy results in greater reductions in hemoglobin A1c at 3 and 6 months than later (12 and 24 months). This may be due to the challenge of maintaining carbohydrate restriction, which is even more evident in very low carbohydrates diets, such as the ketogenic diet (Goldenberg et al., 2021). To circumvent this and improve dietary adherence, the present study assumed a lower carbohydrate restriction, consisting of 40% of the energy intake, which also has demonstrated benefits in metabolic control in patients with T2DM during 8 weeks (van Zuuren et al., 2018).

Also, the currently available studies have some methodological flaws, such as non-randomized or uncontrolled clinical trials (Kindlovits et al., 2022) and insufficient supervision of the reasons for non-adherence to prescribed LCDs (McArdle et al., 2019). These limitations make it difficult to translate their results into clinical practice.

Few studies have analyzed the effects of EH on glycemic and lipid profiles, on cardiorespiratory physiology or on angiogenesis in T2DM (Kindlovits et al., 2022). Furthermore, none of them evaluated HIF1-α levels, which is frequently destabilized in patients with T2DM (Thangarajah et al., 2010). Experiments on cells bearing inactivating mutations in the HIF pathway have emphasized the importance of HIF1-α on the regulation of genes involved in angiogenesis (Iyer et al., 1998; Krishnamachary et al., 2003). Considering that high glucose levels, common in patients with T2DM, impairs the activity of HIF-1α (Thangarajah et al., 2010), EH could be particularly beneficial to improve angiogenesis in this population, because the low oxygen availability in EH further enhances the production of HIF-1α to a greater extent than when training under normoxia conditions (Lundby et al., 2009; Robach et al., 2007). This in turn regulates VEGF expression (Li et al., 2019), appearing to be a key element in the EH-induced adaptations.

This study presents some novelties that make it stronger, such as: (a) it is the first study that will evaluate the serum levels of HIF1-α in T2DM, before and after exercise in normoxia and in hypoxia, with or without a restricted carbohydrate intake; (b) it is the first RCT that will compare the influence of exercise in normoxia with EH, associated or not with LCD, on the glycemic, lipid profile, body composition, blood pressure and cardiorespiratory parameters; (c) our hybrid intervention (EH + LCD) has not been tested together before or compared with other treatment modality (EH); (d) it is the first study to evaluate the effect of both aerobic and strength exercises in hypoxia associated with dietary control in patients with T2DM.

